### Study procedures

#### Informed consent

Informed consent will not be required for the data extraction element of the study as patients will not be directly approached and their data will be extracted pseudonymously. However, the Caldicott Guardian of each participating practice will be required to consent to the extraction. A summary of the method of consent for each study element is provided in Table 2.

**Table 2 Tab2:** Summary of method of consent per study element

Study Element	Method of Consent
Complete questionnaire booklet and link with routine clinical data (patients)	Written via mail-out
Interviews - Face-to-Face	Written
Interviews - Telephone	Verbal
Observations - SSME Session	Written
Observations – Consultations/Meetings	Verbal

All members of the research team receiving informed consent will be Good Clinical Practice certificated, and authorised to do so by the Chief Investigator. Original signed consent forms will be retained and participants will be given or sent a copy. The PIS will detail the exact nature of the study, the implications, and any risks involved in taking part.

#### Consent to complete questionnaire booklet and link with routine clinical data

Patients will be approached by postal invitation sent from the practice along with information about the study and a questionnaire booklet containing a short questionnaire and consent form. Patients will also be asked to provide consent for the research team to link their responses to the data extracted from GP practices and their record held by the local SSME provider, if such a record exists. Patients will be able to decline participation, or to indicate willingness to participate in either the self-report and data linkage (participation in one of these does not necessitate participation in any other activity). Patients could also opt to complete an additional questionnaire which included patient reported outcome measures.

#### Consent to interviews

Informed consent will be received by a member of the research team when a patient or stakeholder agrees to participate in an interview. All participants will have the opportunity to discuss the purpose of the interview and the PIS, ask any questions they have, and then to decide whether they will participate. For face-to-face interviews, the interviewer will obtain written informed consent immediately prior to the interview. For telephone interviews, the interviewer will audio record the reading out of the latest approved version of the consent form and the participant’s agreement with clauses, the consent form will then be annotated with the recording identification code, signed, and dated by the interviewer. The original copy of the consent form will be retained in the study file and a copy will be provided, either at the time of the interview or by post, to the participant.

#### Consent to observation of SSME sessions

The educator(s) of a sample of one-to-one or group-based SSME sessions will be given a copy of the stakeholder PIS and will have the opportunity to consider this information and ask any questions. They will then be asked to provide written consent and confirm the dates of the sessions they would be happy to have observed. If the educator(s) does not consent then no participants will be approached. After educator consent has been received, when booking participants onto one of these sessions, the SSME administrator will inform each participant verbally about the study and the presence of an observer. If a participant does not want to attend a session that is being observed, they will be booked onto a session on an alternative date. Participants who give verbal consent (when booking) to be observed will be sent a PIS. Immediately prior to the session, a verbal delivery of the PIS will be given by the researcher. Prior to requesting written consent, potential participants will be given the opportunity to have any questions related to the study or their participation within it addressed.

#### Consent to observation of healthcare consultations

The ethnographic team will attend clinics in order to observe consultations where discussions about SSME may take place between patients and HCPs. It will not be practical or appropriate to obtain written consent from the HCP or the patient on the day, as this would present a burden to the practice and introduce delays in the clinic/appointment schedule. Therefore, verbal permission will be obtained from the patient and the HCP ensuring that those who wish to opt out can easily make this known. Written and verbal versions of the PIS will be provided and all participants will be given time to consider the information and ask questions. Patients will be informed of the possible presence of an observer by the practice receptionist when they arrive for their appointment. It will be made clear that they are free to ask that their consultation is not observed. The observer will offer to withdraw without any reason having to be given by either the patient or the HCP, and in any event will withdraw if there is any doubt about the appropriateness of their presence.

#### Consent to observation of practice/provider meetings

A sample of meetings where SSME is discussed may be observed. Verbal consent will be sought from the appropriate person in the organisation and/or the Chair of the meeting. When possible, those due to attend the meeting will be informed about the study by the observer prior to the meeting, by providing them with a copy of the stakeholder PIS. If the Chair is willing, at the start of the meeting the observer will explain their role, that anonymity is guaranteed and that they will absent themselves at any time if anyone would rather they were not there; they will then receive verbal consent from all those present. If any individual does not wish to give consent, the observer will withdraw from the meeting. Participants may also request that the observer withdraws temporarily, for example if part of the meeting relates to issues that are confidential, or are not pertinent to the focus of the study. The researcher will respect all such requests.

#### Data collection

Provider-level process outcome data will be collected from the provider using a brief questionnaire at months 0, 9, 18, and 30. Patient-level biomedical and process outcome data will be collected through pseudonymous extraction from primary care data using Read codes. These data will be aggregated where appropriate to calculate the practice-level process outcomes. Data will be extracted at three time-points (month 0, month 9 and 18 collected together, and month 30).

Data extraction procedures are based on those used previously in similar studies [24], and the preceding feasibility study (Davies et al. Increasing uptake of self-management education programmes for type 2 diabetes in a multi-ethnic primary care setting: A feasibility study. 2019. In preparation). Practices can extract their own data, pseudonymise it and then transfer it electronically to the study team at the University of Leicester, or this can be done remotely by PRIMIS. Data extraction will be performed using MIQUEST software. The only key identifier to be extracted will be NHS numbers which will be encrypted into a unique hash (#) code by an Open-Pseudonymiser and CHART software and stored in a spreadsheet containing only pseudonymised data. This will be appropriately and securely transferred to the research team at University of Leicester. PRIMIS will not be able to identify patients at any point during the study. The practice ID code will not be encrypted as it will be required by the study team to identify which randomisation arm the data belong in.

The transferred spreadsheet will contain one line per patient pseudonymised data from all people with T2DM registered at the participating practices during each step (See Table 3). Data recorded over the measurement periods (months 0, 0–9, 9–18, and 18–30) will be extracted.

**Table 3 Tab3:** Data extracted from primary care at each time point

Variable	Value of Interest	To be extracted
Type 2 diabetes diagnosis	First recorded	Value and date
NHS number	Last recorded	Pseudonymised value
Age	Last recorded	Value
Sex	Last recorded	Value
Ethnicity	Last recorded	Value
Smoking status	Last recorded	Value and date
SSME: Referred	Last recorded	Value and date
SSME: Not suitable	Last recorded	Value and date
SSME: Declined	Last recorded	Value and date
SSME: Did not attend	Last recorded	Value and date
SSME: Not completed	Last recorded	Value and date
SSME: Attended	Last recorded	Value and date
SSME: Completed	Last recorded	Value and date
HbA1c	Last recorded within measurement period	Value and date
Body mass index	Last recorded within measurement period	Value and date
Weight	Last recorded within measurement period	Value and date
Height	Last recorded	Value and date
Total cholesterol	Last recorded within measurement period	Value and date
LDL cholesterol	Last recorded within measurement period	Value and date
HDL cholesterol	Last recorded within measurement period	Value and date
Systolic blood pressure	Last recorded within measurement period	Value and date
Diastolic blood pressure	Last recorded within measurement period	Value and date
Cardiovascular risk score	Last recorded within measurement period	Value and date
Medication: Glucose lowering	All recorded within measurement period	Value and date
Medication: Lipid lowering	All recorded within measurement period	Value and date
Medication: Blood pressure lowering	All recorded within measurement period	Value and date
Hospital admission	All recorded within measurement period	Value and date

Each questionnaire booklet sent to patients via a practice mail shot will be pre-assigned a unique patient identifier. Consent and patient details (NHS number, patient name and contact details) will be collected on a separate form and will be stored separately. If the questionnaire booklet is completed and returned with consent, the NHS number will be used to identify the individual patient data in the data extracted from primary care. PRIMIS will provide the study team with the encryption algorithm so a NHS number can be converted to the unique hash (#) code to allow this linkage. Additionally, if consent is given, the list of names and NHS numbers of patients will be cross-checked against relevant provider systems, and data on SSME invitation and attendance held by the provider for these individuals will be linked with their GP and self-report data. The study team will only have access to the name and NHS number of patients returning their questionnaire booklets and will only link data of consenting patients. Secure NHSmail service will be used. Patient NHS numbers will be sent between NHSmail and NHSmail addresses. In addition, list of patients’ NHS numbers will be password protected and passwords will be sent in a separate email. The flow of patient data is shown in Fig. 2.

**Fig. 2 Fig2:**
[figure not shown]
The flow of patient data

#### Integrated ethnographic study

Ethnographic data collection is likely to include observations of: ‘usual care’; implementation of the Embedding Package; and observations of the operationalisation of the Embedding Packing in a variety of local contexts. This will include informal discussions with healthcare, commissioning, and administration staff, the collection of key documents, including publically available information, and structured field notes, [25]; semi-structured interviews (involving stakeholders involved in commissioning, training and implementing SSME and/or the Embedding Package, and people with T2DM). Interviews will explore perceptions and experiences related to the various elements of the Package, and preferred modalities of SSME (such as group-based, one-to-one or online). Interviews will last approximately 30–45 min and may be conducted at their place of work, home, another convenient location, or by telephone, depending on participant preference. All interviews will be audio-recorded (with participant consent) and transcribed.

#### Cost-effectiveness data collection

The ‘Embedder(s)’ (i.e. the person(s) responsible for driving the implementation of the Embedding Package) will complete a simple tick-box tracker of the pre-identified implementation activities for months 0–9, 9–18 and 18–30. This tracker will cover the type of activity, the duration over which it was applied, and whether it is still ongoing, providing a census of what activities have been attempted. In addition, the tracker data will provide a measure of resource use against which unit costs can be applied to estimate the costs associated with the Embedding Package. The unit costs will be generated by structured interviews undertaken with designated staff at provider organisations within a sub-sample of practices. The interview will ask for details of staff time, consumables, and other costs that have been devoted to each individual activity over the duration that the activity was undertaken. A pro-forma for the activity data requirements will be sent in advance of the interview. A follow-up e-mail to confirm the data discussed at the meeting will be sent to the interviewees. A maximum of two further e-mails will be sent to resolve any outstanding data queries. Resource use and costs data for developing the intervention, the Embedding Package, will be obtained from the study team.

### Intervention

The Embedding Package underwent development based on a range of qualitative and experiential work, as well as piloting in an earlier feasibility (Davies et al. Increasing uptake of self-management education programmes for type 2 diabetes in a multi-ethnic primary care setting: A feasibility study. 2019. In preparation). It comprises four key components: 1. clear marketing strategy for SSME; 2. user friendly and effective referral pathways; 3. new/amended roles including a local clinical champion and an ‘Embedder’; 4. toolkit of resources (for patients, HCPs and other key stakeholders). The toolkit contains a wide selection of patient-facing resources (e.g. promotional posters, invitation letters and self-referral forms), HCP-oriented resources and guidance (e.g. document templates, guidance for recruiting staff, referring patients and increasing staff engagement) and coordination/provider/commissioner-oriented resources (e.g. audit collection and reporting, electronic administration and referral systems, and sample referral pathways). It will also include guidance on constructing and carrying out marketing and communication strategies, how to carry out local needs assessments, as well as detail about how to ensure patient accessibility and course tailoring. The new/amended roles will include the appointment of an ‘Embedder’ working across each site (or potentially up skilling of an individual already holding an analogous post) who will liaise between all relevant stakeholders to promote SSME, use of the Toolkit, communication and referrals etc. A local clinical champion in each CCG (for example the Diabetes Lead at one of the participating practices) will be identified to promote SSME across the whole locality. Together the two roles and the online Toolkit make up the ‘Embedding Package’ (the intervention).

Patients will also be able to access online versions of SSME as a complement to attendance at the group-based version as some patients may prefer education delivered via a different modality. In order to track the use of this, practice-specific log-ins will be generated that participating practices can give to patients. There will be posters in participating practices to make patients aware of this option.

To allow for any changes to the landscape of the NHS during the project, whilst maintaining the integrity of the study, any changes to the Embedding Package will only be made at Month 9, i.e. when the wait-list group begin receiving the intervention, so that the Embedding Package received during any one time period is consistent. The details of the Embedding Package that is actually delivered in each time period will be recorded and considered in secondary analyses, as appropriate.

On commencement of the study in a CCG, the Embedder will hold a Toolkit Action Plan meeting to look at which elements of the Toolkit can be implemented. This will then be written up and circulated for finalisation including assigning of tasks to relevant personnel. Review meetings will be scheduled to look at progress. Actions relating to practices will then be disseminated by the ‘Embedder’ to the relevant staff within each practice, and additional meetings arranged, if necessary.

### Control

Usual care will be practice-dependent; therefore, each practice will continue to provide their usual activities related to SSME whilst in the control period. These activities vary greatly between CCGs and their associated practices, and due to the ever-changing landscape of the NHS, usual care may evolve over time. However, usual care will be monitored and recorded within all practices.

### Randomisation

This is an open-label trial as it will not be possible to blind practices to their treatment arm. Practices will be randomised prior to baseline (month 0) in a 1:1 fashion to either: Immediate group (receive the Embedding Package for months 0–18), or wait-list group (provide usual care for months 0–9 then receive the Embedding Package for months 9–18). Randomisation will be stratified by CCG, and generated and implemented by a statistician. The statistician will provide the study team with the randomisation outcome so that they can inform practices of their allocation.

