### Analysis methods

#### RCT

Data from the RCT will be analysed once data collection is complete. Descriptive summary statistics of baseline characteristics and process variables (e.g. number of education sessions available, back end data for the Toolkit and MyDesmond websites, usual care delivery, etc.) will be produced, using mean (standard deviation) for normally-distributed variables, median (interquartile range) for non-normally distributed variables, and count (percentage) for categorical variables.

The primary analysis will compare HbA1c between the control and intervention states using a mixed model that allows for repeated longitudinal outcomes and practice-level clustering, and is adjusted for season to deal with expected seasonal variation in HbA1c. The primary analysis will be based on the intention-to-treat (ITT) population, i.e. all eligible patients will be included. Missing outcome data will need to be imputed for the ITT analyses. This will be done using an appropriate multiple imputation method; it is anticipated that predictive mean matching will be used to impute continuous outcomes as this is able to handle non-linearity and non-normality, and logistic regression will be used for binary outcomes. Predictive variables are likely to include practice level demographics, e.g. sex, ethnic group, or baseline HbA1c. Sensitivity analyses will repeat the primary analyses using complete cases and per protocol populations.

As secondary analyses, the ITT model from the primary analysis will be fitted for the following subgroups of interest: (1) including only patients who attended education; (2) excluding patients with HbA1c < 6.5% at baseline; (3) by baseline education attendance status; (4) by patient ethnicity and age to examine the effectiveness of the Embedding Package in groups in which there is low SSME uptake; (5) by type/format of programme offered/attended.

Secondary patient-level and practice-level outcomes will be compared in a similar manner to the primary analyses, except that practice-level outcomes will not be adjusted for cluster and the psychosocial outcomes will not account for repeated measures as they will only be measured once.

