Summaries of self-reported referral and attendance will be produced using appropriate descriptive statistics for the whole dataset and by pertinent subgroups, such as sex and age. Data on SSME referrals and attendance will also be compared between data sources (i.e. self-report, practice, and provider).

A full statistical analysis plan will be written and agreed by all investigators and the trial steering committee before the data are released for analysis. Statistical significance will be defined as *p*-values less than 0.05.

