### Sample size

In the feasibility study an average cluster size of 460 was found across the six practices included (range 118–824) (Davies et al. Increasing uptake of self-management education programmes for type 2 diabetes in a multi-ethnic primary care setting: A feasibility study. 2019. In preparation). Recruiting 58 practices (29 to each randomisation point) will give over 90% power to detect a difference in HbA1c of 0.1% assuming an SD of 1.5%, based on United Kingdom Prospective Diabetes Study (UKPDS) [35]. There will be 80% power to detect a difference as small as 0.062%. This assumes an intra-cluster correlation coefficient (ICC) of 0.05, one baseline HbA1c measurement with one more HbA1c measurement at each randomisation point. This calculation does not take account of potential variation in cluster size, as methodological work has shown that the power of studies of a stepped wedge type design is robust to variation in cluster size [36]. The sensitivity of this calculation to changes in the average cluster size was assessed. As long as the average cluster size remains larger than 174 there will be 80% power to detect a 0.1% difference. To allow for potential cluster drop out of 10% the target will be to recruit 66 practices in total.

Return of a completed questionnaire booklet (self-report questionnaire and/or consent to link data form) will be recorded as consent to participate in the study. Additionally stakeholders and patients consenting to ethnographic interviews and observations will be recorded as participants. It is anticipated a minimum of 2050 participants will be recruited (2000 via questionnaire and 50 via interview/observation).

The integrated ethnographic study will be conducted within a sub-sample of approximately 12 of the practices and related contexts (e.g. CCGs and providers). Purposive sampling of practices will take place in the first and second steps of the RCT to ensure a representative sample [22]. A subset of 12 practices will provide data for the cost-effectiveness analysis.

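### CCG, the stratification factor, is not among the model terms the article names; for the once-measured psychosocial outcomes this would overstate standard errors and lose power, while for primary HbA1c it hardly matters

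*Protocol article*

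**What the plan says.** The Randomisation section of the protocol article says "Practices will be randomised prior to baseline (month 0) in a 1:1 fashion", and that "Randomisation will be stratified by CCG, and generated and implemented by a statistician". No other stratification factor is given, and the number of CCGs is not stated.

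The RCT part of Analysis methods describes the primary analysis as a "mixed model that allows for repeated longitudinal outcomes and practice-level clustering, and is adjusted for season". Secondary outcomes are to be handled in a similar way, with two exceptions: "practice-level outcomes will not be adjusted for cluster and the psychosocial outcomes will not account for repeated measures". CCG is named in none of these models. The article does not say that CCG will be left out, and it adds that "A full statistical analysis plan will be written and agreed by all investigators and the trial steering committee" before data release.

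The article also gives reasons to expect CCG to matter. The Control section says of usual SSME activities that "These activities vary greatly between CCGs and their associated practices". Under RCT design and Intervention, some components are aimed at CCG, locality or provider level, and each CCG has a local clinical champion.

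**The concern.** Stratifying by CCG balances the two arms within each CCG. If outcomes differ between CCGs, that balance lowers the true variance of the treatment comparison. A model without CCG does not recognise the reduction: it leaves CCG differences in the between-practice variance and computes the standard error as if they could have fallen unevenly between arms. Reported intervals are then too wide, and tests reject too rarely.

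How far this matters depends on the type of comparison. HbA1c is measured at baseline and in both steps, so most information on treatment comes from within practices, where a constant CCG difference cancels. The patient activation, well-being and diabetes-distress scales are collected once, in the first step, and compared between immediate and wait-list practices. That comparison is entirely between practices, with no own-control period to remove CCG differences. What is at stake is power for these secondary outcomes.

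**Working it through.** **Reproducing the planned power.** Inputs from Sample size: 58 practices in two sequences of 29, mean cluster size 460, ICC 0.05, SD 1.5%, one baseline and two steps. Alpha is 0.05, taken as two-sided because sidedness is not stated. The standard stepped-wedge variance (Hussey and Hughes: fixed period effects, random practice intercept) gives a standard error of 0.02185.

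- Power at 0.1%: 99.6% (stated: over 90%).
- Power at 0.062%: 81.0% (stated: 80%).
- Power at 0.1% with cluster size 174: 80.8% (stated: 80%).

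The plan's figures reproduce, so this model is a fair basis for the next step.

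**Primary HbA1c.** Take 66 practices, arranged by assumption as 11 CCGs of 6 with allocation balanced in each. Split the practice variance into a CCG part and a within-CCG part, with the CCG share varied from 10% to 75%.

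- Standard error reported without CCG: 0.02048.
- True standard error of that same analysis: 0.02048 down to 0.02043, so the overstatement is 0.03% to 0.25%.
- Standard error with CCG as a fixed effect: 0.02048 down to 0.02029, a gain of at most (0.02048 − 0.02029)/0.02048 = 0.9%.

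**Psychosocial outcomes, measured once.** With total variance 1, m respondents per practice and CCG share s of the between-practice variance:

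- Variance of a practice mean as the model without CCG sees it: ICC + (1 − ICC)/m.
- Variance relevant after balancing by CCG: (1 − s) × ICC + (1 − ICC)/m.
- Overstatement of the standard error: the square root of the ratio, minus 1.

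About 2000 questionnaires over 66 practices is 30.3 per practice. That is an upper figure for these scales, because they come only from the optional additional questionnaire. The share of patients completing it is not given, so 15 and 10 per practice are also tried. ICC 0.05 is borrowed from the HbA1c calculation, and s = 0.5 is assumed.

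| m | Without CCG | After balance | Square root of ratio | Overstatement |
|---|---|---|---|---|
| 30.3 | 0.0814 | 0.0564 | 1.20 | 20% |
| 15 | 0.1133 | 0.0883 | 1.13 | 13% |
| 10 | 0.1450 | 0.1200 | 1.10 | 10% |

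The usual design-effect shortcut, sqrt{[1 + (m − 1) × ICC]/[1 + (m − 1) × ICC × (1 − s)]}, gives slightly less:

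- m = 30.3: sqrt(2.47/1.73), or 19%.
- m = 15: sqrt(1.70/1.35), or 12%.
- m = 10: sqrt(1.45/1.225), or 9%.

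Hence roughly 9% to 20%.

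**Consequence.** At 30.3 per practice, ICC 0.05 and s = 0.5, the actual two-sided alpha is 0.019 instead of 0.05. A comparison with 80% power under the adjusted analysis has 67%. At 10 per practice the same formulas give an alpha of 0.031 and 74% power.

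**Sensitivity at 30.3 per practice.**

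- ICC 0.05: 3%, 9%, 20% and 36% for CCG shares of 10%, 25%, 50% and 75%.
- ICC 0.01: 1% to 10% over the same shares.
- ICC 0.10: 4% to 54%.

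**The case against.** The strongest objection is that the article is silent on CCG and does not exclude it. It condenses a fuller plan and defers to an SAP that is not shown, and stratification factors are often listed there. This stands as a limit: one can say only that no analysis described in the article includes CCG, not that none will. The point survives because the article does list its model terms and the exceptions for secondary outcomes, and following that description as written is worse for once-measured outcomes.

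Four stronger readings are tempting, and the documents do not support them.

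- **That the primary result is at risk.** A sizeable gain for HbA1c can be produced by assuming a cluster autocorrelation of 0.9, with half of the resulting practice-by-step variance shared within CCG. CCG-by-step terms would then cut the standard error by about 20%: sqrt[(0.005625 + 0.004647)/(0.01125 + 0.004647)] = 0.80. The article gives neither quantity, and its sample size model has no such variance component.
- **That the standard errors threaten validity.** Given balance within CCG, the error runs in the conservative direction.
- **That the stratification is wasted.** Balance by CCG is kept and still lowers the true variance. Only the credit for it in the analysis is lost.
- **That dropping the cluster term for practice-level outcomes is itself wrong.** With one value per practice, the practice is the unit of analysis and a practice term is not needed. Practices in a CCG may still share a provider, so CCG belongs in these models too, but ignoring it is again conservative under balanced allocation.

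The Control section also describes usual care as depending on the practice. It supports CCG as a plausible prognostic factor but does not fix the CCG share of variance.

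**Conclusion.** The point holds in a limited form. The models described do not use the only stratification factor, and for outcomes compared solely between practices this gives standard errors that are too large if CCG is prognostic. For the psychosocial scales the excess is roughly 9% to 20% at ICC 0.05, with half of the between-practice variance at CCG level and 10 to 30 respondents per practice. The ICC for these scales, the CCG share, the number of CCGs and the uptake of the additional questionnaire are not in the article, so this is a range under assumptions and not an estimate. For practice-level outcomes the direction is the same, but no size was computed. For primary HbA1c the effect is under 1% under the planning assumptions, and the power statement is unaffected. This is a modest point about efficiency in secondary outcomes.

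**What to change.** State in the SAP, before data release, that CCG enters the primary and secondary models as the stratification factor. Use a fixed effect, or a random effect if there are many small CCGs. The psychosocial and practice-level models need it most; in the HbA1c model it keeps the analysis consistent with the randomisation at almost no cost.

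The cost is one sentence and one degree of freedom per CCG beyond the first. With the 11 CCGs assumed above that is 10, leaving 66 − 2 − 10 = 54 between-practice degrees of freedom for a once-measured outcome.

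CCG-by-step terms should not be required. With 11 CCGs and three periods, main effects plus interaction add 10 + 20 = 30 parameters for 66 practices. At most they belong in a sensitivity analysis.
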